## Abstract

**Background:**

Screen time among children and adolescents has increased dramatically, raising concerns about its impact on development and mental health. While research highlights both potential benefits and risks, excessive use has been linked to issues like anxiety, depression, and gaming addiction. Despite growing concern, effective interventions are scarce. Recognizing the importance of family dynamics in child development, we propose a family-centered program to address problematic gaming and excessive screen use in a clinical population. By involving both children and parents, we aim to create a more comprehensive approach to prevention and treatment.

**Objective:**

This study aims to determine the possibility of distributing and evaluating a family-centered group program for problematic gaming and excessive screen use (FAME) in a clinical child and adolescent psychiatry (CAP) population. We will monitor the recruitment rate; track the retention and attendance rates of both parents and children; and assess whether each session’s objectives are met, the content is delivered within the allotted time, and the necessary resources (eg, facilitators and materials) are available. Additionally, we will gather qualitative and quantitative feedback from participants through postprogram surveys and individual interviews with both children and parents.

**Methods:**

A total of 10 families with ongoing contact with CAP in Skåne, Sweden, will be recruited and offered participation in a family-centered group program targeting children aged 10-18 years with reported difficulties regarding screen gaming or screen use. The intervention to be tested is a newly developed, family-centered, psychoeducational, cognitive behavioral therapy–based intervention addressing both positive and negative aspects of screen use; setting boundaries; the connection between thoughts, feelings, and behaviors; conflict triggers; and sleep hygiene. The primary goal of the pilot study is to test the feasibility of the program, as well as recruitment and the analysis of participants’ experiences with the program.

**Results:**

A total of 11 children and their parents were enrolled during first quarter of 2024. A 4-session pilot was delivered in first quarter of 2024, and the first results are expected in the third quarter of 2024.

**Conclusions:**

The overarching goal of this pilot study is to determine the possibility of distributing and evaluating a family-centered group program for problematic gaming and excessive screen use (FAME) in a clinical CAP population. The insights gained from this study will guide our future research, which will focus on conducting a larger-scale evaluation of the intervention’s impact on family screen time conflicts and inform future strategies for the implementation of family-centered interventions in child and youth clinics.

**Trial Registration:**

ClinicalTrials.gov NCT06098807; https://clinicaltrials.gov/study/NCT06098807

**International Registered Report Identifier (IRRID):**

DERR1-10.2196/56387

## Introduction

During the past 10 years, the use of screens, as in social media and video games, has become one of the most common leisure activities for children and adolescents. According to the Swedish Internet Foundation, 94% of children in Sweden between ages 8 and 12 use screens every day [1], with boys playing video games while girls being more active on social media [2]. The growing trend of children and youth spending excessive amounts of time engaged with screens has been perplexing adults. Parents and professionals who work closely with children and youth are particularly concerned about the potential negative impacts of screen time on their overall development [3-5]. Some research suggests that screen time in general and gaming in particular is an educational and skills training activity that can stimulate the user’s cognitive abilities and ability to solve problems [6]. Other research has concerns that screen use can become a potentially pathological activity that interferes with everyday life with risks of developing psychiatric disorders such as social media disorder or internet gaming disorder (IGD) [7]. Indeed, while there is currently no official diagnosis for social media disorder, IGD is included in the *Diagnostic and Statistical Manual of Mental Disorders, Fifth Edition*, as a condition necessitating further clinical experience and research before inclusion as a formal disorder. The World Health Organization, on the other hand, has included gaming disorder in the *International Classification of Diseases, 11th Revision*, as a formal diagnosis [8].

Screen time for adolescents is a complex issue. While it is often associated with gaming, it encompasses a wider range of activities like social media, communication, and even creative pursuits through apps. Social media use, for instance, can foster positive digital behavior and a sense of belonging [9,10]. However, research also indicates that excessive screen time can negatively impact mental health, leading to anxiety and depression in young people [11]. The increasing presence of social media in teenagers’ lives presents a double-edged sword. Moderate use can be beneficial for social-emotional development and peer relationships. However, problematic social media use, characterized by addictive tendencies and an inability to regulate use, has been consistently linked to depression, anxiety, and stress [12,13]. While not a formal diagnosis, it is often evaluated based on such addictive symptoms [14].

There is a general consensus among school health professionals, social workers, child and adolescent psychiatrists, and even parents that excessive screen time can impact childhood development [15]. However, clear recommendations remain elusive. Many parents allow their children’s current behavior, believing that media content can be educational and that screen time offers a readily available, affordable form of entertainment [16].

Experiencing addictive problems as a child may pose a threat to future psychosocial development [17], including mental health and socioemotional development. In that sense, child and youth mental health services need to put more effort into developing interventions that target children at risk to prevent the development of mental health problems among children and youth. To date, there are no evaluated preventive programs for children and youth with excessive screen time, including problematic gaming, in Sweden.

Our research group from Lund University and Region Skåne has evaluated relapse prevention as an individual treatment for problematic gaming in a randomized controlled trial among children aged 12-18 years in a child and adolescent psychiatry (CAP) setting [18]. This was one of the first treatment studies for children with problematic gaming in Europe. Although we discovered that the individual treatment of children and youth has a promising effect on their gaming, we also found that important pieces were lacking when providing treatment for children with problematic gaming. The most prominent one was the lack of family, including parents, involvement in the treatment. Indeed, children and their development need to be seen from a system perspective [19]—children develop interaction with their environment or family. For children, parents are the closest socializing agents in their environment, who, with their parenting behaviors and practices, pave the way for child developmental transitions. In that sense, the development of certain behaviors, such as gaming and excessive screen use, may, at least to some extent, be related to family factors [20,21]. It is then possible that a child’s problematic screen time or gaming is not only attributed to the child itself, but to the family as a system. Therefore, we believe that parents need to be included in the preventive interventions targeting children and their families. Instead of only focusing on the child, changing the family environment, including parent-child interactions at home, may pose significant changes in the child’s screen behavior. This is a recognized logic from other family interventions such as the Strengthening Families program targeting families with children with behavioral problems [22] and the Cool Kids program [23] targeting families with children with anxiety. In fact, parents whose children have undergone the relapse prevention treatment in our project state that they need to and want to be involved in the child’s treatment. Arguments for family-centered interventions in the treatment of IGD have been presented in previous compilations and emphasize experiences from addiction conditions, where family system involvement has been shown to be important in bringing about behavioral changes in the child [24]. Additionally, group-based treatment shows promise for adolescents with problematic gaming [25], although the underlying mechanisms need further exploration. Problematic screen use, not the least gaming, is particularly shown in children with neurodevelopmental disorders, such as attention-deficit/hyperactivity disorder and autism spectrum disorder [3,26], and we, therefore, consider it crucial to evaluate the intervention in a clinical setting where these children are present.

The objective of this study is to determine the possibility of distributing and evaluating a family-centered group program for problematic gaming and excessive screen use (FAME) in a clinical CAP population. We will examine the feasibility of the program including treatment delivery and recruitment of the participants. Additionally, we also aim to examine the participants’ experience of the program, as well as the relevance of the selected measuring instruments. The conclusions drawn from this study will serve as the foundation for a larger, quasi-experimental study in a clinical setting to follow.

## Methods

### Overview

The family-centered program for problematic gaming and excessive screen use in a child and youth population (FAME; [name], unpublished data, 2024) is a group-centered, family program developed and based on theoretical and empirical knowledge of parenting and child and youth development [19-21]; knowledge from the previous randomized controlled trial study on individual treatment of child and youth gaming problems [18]; and findings from interviews with the parents regarding their needs and content aspirations relating to gaming and excessive screen use.

The program specifically targets families where the child exhibits excessive screen use including problematic gaming and social media use. Both the child and at least 1 parent participate in the program, with the main goals being (1) to reduce problematic and excessive screen use in children and (2) to strengthen parent-child relationships. The logic model behind the program (Textbox 1) illustrates that these goals are achieved through various components such as psychoeducation, cognitive restructuring, and social and emotional learning. The theoretical framework is based on systemic theory [27], social cognitive theory [28], and emotion socialization theory [29]. The psychoeducational elements consist of information on screen-related health, sleep hygiene, and supportive interactions with children with mental health issues and are conveyed and illustrated through video clips, the use of a shared whiteboard, and illustrative example situations. The program uses different activities, including storytelling and on-site and home assignments, to help children and parents understand the positive and negative aspects of screen use, recognize cognitions and emotions, and prevent problems and family conflicts (proximal goals). Additionally, the program aims to teach participants how to handle emotions and behaviors as mediating mechanisms, ultimately leading to the attainment of the main or distal goals.

The program includes an initial individual session (session 0) where the child and the participating parent or parents meet with a clinician for goal setting and a motivational interview. This is followed by four group sessions with the following content: (1) positive and negative aspects of screen use and structure for setting boundaries; (2) psychoeducation on how thoughts, feelings, and behaviors influence each other and strategies for emotion regulation; (3) identifying triggers and preventing conflicts; and (4) psychoeducation on sleep hygiene and continued work moving forward.

Group session 1, conducted separately for children and parents, begins 1 to 2 weeks after session 0. Although the themes in both child and parent groups are aligned, the activities and outputs are tailored to be age appropriate and meet the specific needs of children and parents.

The sessions will take place at a CAP clinic that serves both subclinical and clinical groups of patients. The program will be delivered by clinicians, who could be doctors, psychologists, or health counselors, all possessing competence in cognitive behavioral therapy and having completed a 2-day FAME program education.

Each session is expected to last approximately 90 minutes, including a 15-minute break. This timeframe allows for a comprehensive and effective delivery of the treatment.

Logic model of the FAME program.
**Target group**
Families seeking support for problematic screen use in children
**Theory**
Family system theorySocial cognitive theoryTheory of emotion and emotion-focused therapy
**Components**
PsychoeducationCognitive restructuringEmotional knowledge and regulationParenting skills
**Activities**
Meeting sessionsDiscussionsStorytellingPractice and homework
**Outputs**
One individual meeting with the clinicianFour group sessions with children and parents in separate groupsHomeworkBooklets
**Proximal goals**
Understanding the positive and negative sides of screen useRecognizing feelings and emotional and behavioral triggersPreventing emotional tantrums and family conflicts
**Mediating mechanisms**
Children learn to control their behaviorParents learn to handle (child) feelings and behaviorsEnhanced parenting skills
**Distal goals**
Less problematic screen useBetter parent-child relationships

### Enrollment

Primary care patients (*Första linjen*) seeking treatment at CAP units in Skåne for problematic gaming or excessive screen time will be given the opportunity to participate in our treatment program. Patients contact CAP Skåne through En Väg In, a call center managed by psychiatry nurses and health care counselors. During the standard intake interview, patients are asked “Does your child (or “do you” if the child calls themselves) have any problems related to gaming or screen use?” As part of the existing procedure, parents or children who call En Väg In are also asked if they consent to be contacted for participation in research programs. The responses are tagged by the staff, and these tags are analyzed weekly by research administrators. Families with both tags are then contacted and provided with oral and written information about the study and the program. Families can be included in the study in 2 ways: either by being contacted by the research team during the initial contact with CAP, following the procedure described above, or by their therapist at CAP. Therapists at CAP can contact the study if families have described screen-related family conflicts in the context of receiving other care and have consented to be contacted by the research team for further information about the study. Regardless of the contact method used, research team staff will contact guardians by phone in an initial call to provide information about the study, assess motivation and consent, and verify inclusion and exclusion criteria. If all inclusion criteria are met and no exclusion criteria are present, the family will be scheduled for session 0, the content of which has been described above. For this pilot study, we will enroll 10 families, involving both the child and parent or parents. The inclusion and exclusion criteria are provided in Textbox 2.

Inclusion and exclusion criteria.
**Inclusion criteria**
Age between 10 and 18 yearsReported problems in the family regarding computer gaming or screen useChildren or youth and guardians can read, write, and communicate in SwedishAn available guardian who can participate in the programPossibility to participate in program sessions on-site
**Exclusion criteria**
Observed or suspected intellectual disability

### Measures

The following data will be collected within the framework of this pilot study. The usability of the scales will be evaluated in future analyses. The data given below will be collected from the children:

SCREENS-Q screening form, for valuing children and adolescent’s screen time (adapted version, including questions targeting extent, type of activity, boundary setting, and positive and negative consequences of the child’s screen use): It has shown good internal consistency (Cronbach α 0.61-0.90) [30].Game Addiction Scale for adolescents, for the diagnosis of computer game addiction targeting questions in accordance with the proposedDiagnostic and Statistical Manual of Mental Disorderscriteria for IGD [5]: The instrument has shown good internal consistency (Cronbach α 0.81-0.86) [31].The Kessler Psychological Distress Scale (Kessler-6) screening for depression and anxiety over the past 6 months, including questions regarding feelings of hopelessness and nervousness: It is a widely internationally used measure of psychological distress. The instrument has shown a sensitivity of 0.36 (0.08) and a specificity of 0.96 (0.02) in predicting severe mental illness in a general population [32,33].Parenting Children and Adolescents Scale (PARCA) for assessing aspects of the parent-child relationship and parenting practices (adapted version including questions regarding encouraging positive behaviors and setting boundaries) [34]: This is originally a 19-item measure with each item rated on a 5-point scale. The instrument includes 3 subscales: encouragement of positive behaviors, setting limits, and proactive parenting behaviors, and has shown good psychometric properties (Cronbach α 0.86-0.91) [34].Adult-Child Relationship Scale—Family Check-Up (FCU): It measures warmth and conflict with 8 items rated on a 5-point scale targeting questions such as the tendency to involve parents in the child’s thoughts and feelings and 3 items measure parent-child conflicts and conflict behaviors. Scale α values in previous studies have shown good internal consistency (Cronbach α 0.74-0.85) [35].The Insomnia Severity Index Adolescent for assessing sleep problems: It is a well-established tool for measuring sleep problems in adolescents, including questions targeting the child’s perception of the consequences of their sleep patterns. Scale α values in previous studies have shown good internal consistency (Cronbach α 0.83) [36,37].Background data: gender, age, length, weight, family constellation, parental education level, and diagnosis at CAP.

Baseline data that will be collected from the parents before treatment are:

SCREENS-Q screening form for valuing children and adolescents’ screen time (adapted version, including questions targeting extent, type of activity, boundary setting, and positive and negative consequences of the child’s screen use) [30].PARCA for assessing aspects of the parent-child relationship and parenting practices (adapted version including questions regarding encouraging positive behaviors and setting boundaries) [34].FCU: 5 items measure parent-child warmth such as questions about the parent’s perception of the child’s openness about their thoughts and feelings, and 3 items measure parent-child conflicts and conflict behaviors [35].

Given our expectation that a larger evaluation will be able to determine whether the intervention has any impact on screen-related conflicts within families, we will pay particular attention to the usability of the PARCA and FCU instruments. The follow-up data will be collected in connection with the last session of the program. Interviews with children and parents will be conducted approximately 2 weeks after the end of the program. The interviews will focus on the participant’s experience of the program. The quantitative data will be analyzed with SPSS (IBM Corp), and the interview data will be analyzed with thematic analysis [38].

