### Analysis

In our analysis, we will be addressing several key indicators such as (1) monitoring the recruitment rate by tracking the number of eligible participants approached versus the number enrolled in the study; (2) tracking the retention and attendance rates of both parents and children; (3) evaluating whether each session’s objectives are met, the content is delivered within the allotted time, and the necessary resources (eg, facilitators and materials) are available; and (4) gathering qualitative and quantitative feedback from participants through postprogram surveys and individual interviews with both children and parents. By assessing these criteria, we will determine if the program and recruitment processes are feasible and ready for expansion into a larger, quasi-experimental study. In order to capture the participants’ experience of the program, semistructured interviews will be conducted and analyzed using thematic analysis [38]. For the statistical analysis, we will use 2-tailed paired sample *t* tests to address potential differences in pre- and postprogram measures. However, if data are not normally distributed, a nonparametric Wilcoxon signed rank test will be used. After each session, group leaders together with the project owner will assess compliance and pay particular attention to any adverse events such as deterioration in family relationships or increasing ill health of the participants. What constitutes an adverse event in psychotherapy can be difficult to define [39], although it could constitute severe illness, parental divorce, etc. We will, therefore, pay particular attention to any of the changes within the individuals and their families in the various parts of the data collection.

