## Results

A total of 11 children and their parents were enrolled during the first quarter of 2024. A 4-session pilot was delivered in the first quarter 2024, and the first results are expected in the third quarter 2024. The results are intended for publication in international peer-reviewed scientific journals and presentation at international and national scientific conferences. A primary publication is planned for the first quater of 2025. Additional secondary publications may follow. Whenever possible, the results will be presented in open-access journals.

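### Kessler-6 asks about the past 6 months but follow-up comes at most about 13 weeks after baseline, so a repeated score would strongly attenuate any change in distress

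*Protocol article*

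**What the plan says.** The Measures section opens the child list with "The data given below will be collected from the children". One entry is the Kessler-6, described as "screening for depression and anxiety over the past 6 months". The child list carries no baseline-only label; the parent list that follows it is introduced as baseline data, and the Kessler-6 is not on it.

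On timing, Measures states: "The follow-up data will be collected in connection with the last session of the program". The Overview under Methods describes an individual session 0 and continues: "This is followed by four group sessions with the following content". It also says: "Group session 1, conducted separately for children and parents, begins 1 to 2 weeks after session 0". The spacing between the group sessions is not given. The Results section places enrolment in the first quarter of 2024 and adds: "A 4-session pilot was delivered in the first quarter 2024".

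On analysis, the Analysis section plans two-sided paired-sample t "tests to address potential differences in pre- and postprogram measures", with a Wilcoxon signed rank test if the data are not normally distributed. It neither names nor exempts any instrument.

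**The concern.** A pre-post comparison can show change only to the extent that the second answer describes a different period from the first. Here the recall period is at least twice as long as the time between the two measurements, so a child answering at the last session is asked largely about months already covered at baseline.

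Two uses of the result are affected. First, the end of the Introduction makes the relevance of the chosen instruments an aim of the study, and Expected Outcomes anticipates that they will prove suitable for evaluating the program. A Kessler-6 score that hardly moves could reflect the recall period, the scale or the program, and the data could not tell these apart. Second, the Analysis section says that changes in participants and families will be looked for across the data collected, as part of attention to adverse events. Among the named child scales, the Kessler-6 is the one aimed at depression and anxiety. A small or null change on it would be weak reassurance.

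**Working it through.** The article states no power, effect size or sample-size figure for this scale, so there is nothing to reproduce. The check is the overlap of the two recall windows.

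**Inputs**
- Recall window R = 6 months, taken as 26 weeks (Measures).
- Session 0 to group session 1: 1 to 2 weeks (Overview).
- Four group sessions, hence three intervals of g weeks each. The value of g is not stated; 1, 2 and 3 weeks are assumed.
- Follow-up at the last session (Measures).
- Baseline taken at session 0. This is assumed; the article says only that parents' baseline data precede treatment.
- Calendar bound: the first quarter of 2024 has 31 + 29 + 31 = 91 days, or 13 weeks, and contains both enrolment and delivery (Results).

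**Formulas**
- Baseline to follow-up: T = (1 or 2) + 3g, and at most 13 weeks.
- Share of the follow-up window after baseline: T / R. Share before baseline: 1 − T / R.

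**Results**

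| Spacing | T (weeks) | After baseline | Before baseline |
|---|---|---|---|
| Weekly (assumed) | 4 to 5 | 4/26 = 15% to 5/26 = 19% | 81% to 85% |
| Every 2 weeks (assumed) | 7 to 8 | 7/26 = 27% to 8/26 = 31% | 69% to 73% |
| Every 3 weeks (assumed) | 10 to 11 | 10/26 = 38% to 11/26 = 42% | 58% to 62% |
| Calendar bound | 13 | 13/26 = 50% | 50% |

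Counted from group session 1 instead of session 0, weekly sessions leave 3/26 = 12% of the window after the start of the group program.

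**What this does to a true change.** Suppose that answers average evenly over the window, that distress was level at m0 before baseline, and that it is m1 from baseline onward. The baseline score reflects m0. The follow-up score reflects (1 − T/R) × m0 + (T/R) × m1. The difference is (T/R) × (m1 − m0), so 15% to 19% of the true change appears with weekly sessions and 50% at the calendar bound. A change that built up gradually would show less; a child who weighs recent weeks more heavily would show more. Under these assumptions the expected difference is reduced but is not zero.

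**The case against.** The strongest reply is that the article never says the Kessler-6 is repeated. The child list also holds one-off items such as gender and parental education, so being listed does not prove re-administration, and the exact stem used at follow-up would sit in material not shown. That stands as a limit on certainty, and the point is therefore conditional. But nothing exempts the scale from follow-up or from the paired tests, and only the parent list is labelled as baseline. If the Kessler-6 was in fact asked once, saying so resolves the matter.

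A second reply is that this is a feasibility pilot of 10 planned families (11 children enrolled) that disclaims conclusions on effect, gives particular attention to PARCA and FCU, and defers the usability of the scales to later analyses. That limits the consequence. It does not remove it, because instrument relevance is one of the pilot's own aims.

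Several stronger readings are tempting but not supported:
- A reader might infer that the comparison cannot register change or harm at all. Between 15% and 50% of the window follows baseline in the scenarios counted from session 0, and children may weigh recent weeks more.
- A reader might infer that the interval is known to be 4 to 5 weeks. That rests on weekly sessions; only the 13-week bound is documented.
- A reader might infer that harm would be missed. Group leaders and the project owner assess adverse events after each session, and interviews follow about 2 weeks after the program ends.
- A reader might infer that the Kessler-6 change will feed the planning of the larger study. No section says so; that study targets family conflict over screen time.
- A reader might turn the attenuation into a multiple of the required sample size. That needs even averaging and an unchanged SD of change, and overlapping windows would probably shrink the SD too. The article has no sample-size calculation for it to affect.

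**Conclusion.** The point holds in conditional form. If the Kessler-6 is repeated with the 6-month stem, at least 50% of the follow-up window precedes baseline, and about 81-85% does if sessions were weekly. The 50% figure rests on the stated recall period, follow-up at the last session, and enrolment and delivery within one quarter. The higher range adds the weekly-spacing assumption and a baseline at session 0. How much of a true change survives depends further on how children average over the period, so those percentages are illustrative.

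The paired comparison for this scale would be strongly attenuated in both directions, and a flat result would not be informative about responsiveness, effect or deterioration. The consequence is confined to one child-reported scale in a feasibility pilot, but the correction is cheap and worth making before the scale is taken into a larger study.

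**What to change.** - State whether the Kessler-6 is given at follow-up and what recall period each administration uses.
- In any further cohort and in the larger study, use the same recall period at both time points, no longer than the baseline-to-follow-up interval T. With R no greater than T, the whole follow-up window falls after baseline. This requires the session spacing to be stated. The time from last session to follow-up cannot serve as the limit, because follow-up takes place at the last session and that gap is about zero.
- For pilot data already collected with the 6-month stem, report the Kessler-6 as a baseline descriptor, leave it out of the pre-post tests, and do not cite its change as evidence of no effect or no deterioration.

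The cost is one altered question stem, one fewer pre-post outcome in the pilot, and less comparability with earlier data that used the 6-month stem.
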